#### Exclusion criteria

Previous treatment for recurrence of disease.Largest diameter of the enhancing lesion of less than 1 cm on the index MRI, usually measured in the axial plane.In the newest RANO PET-criteria, it is advised to use [^18^F]FET PET for increasing lesions only in cases with a minimum lesion size [18].Life expectancy of less than 6 months, determined by the treating physician.Contra-indications for PET (claustrophobia, inability to lay still).Women of childbearing potential without adequate contraception during randomization and possible [^18^F]FET PET scan.Any other concomitant disease that may influence PET imaging or clinical outcomes of this study. This includes but is not limited to cerebral inflammatory diseases and other cancers with brain- or leptomeningeal metastases.

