### Sample size {14}

From current practice (survey among the participating centers), we estimate that 37% of the glioblastoma patients that meet our inclusion criteria, eventually undergo unnecessary interventions (control arm). In the intervention arm, we expect this proportion to be much lower (~ 12% from clinical scenarios), due to the high accuracy of [^18^F]FET PET. Using a two-sided *Z* test with pooled variance with an alpha of 0.05, based on a power of 90%, we need 61 patients in each arm, so 122 in total. Due to the intention-to-treat set-up and unnecessary treatment as outcome measure, we expect that virtually all patients can be included in final analysis, with minimal drop-out. For the co-primary endpoint of HRQOL (EORTC-QLQ-C30 + BN20) at *t* = 12 weeks, drop-out due to missing questionnaire data is estimated at 10%. With addition of this drop-out rate, we will randomize 144 patients, 72 patients per study arm.

Methodologically, the two primary endpoints are hierarchical: the first (unnecessary interventions) must be met before the second (HRQOL) is formally tested. Since HRQOL may be influenced by earlier diagnosis from FET PET, the primary endpoint of unnecessary interventions should be met first to obtain a HRQOL result which is not caused solely by such a timing effect. This justifies a fixed-sequence testing approach—each tested at *p* = 0.05. If the first test is not significant, HRQOL results will be considered exploratory. The sample size was powered for the first endpoint, with a 10% increase to account for potential missing HRQOL data; a formal power calculation for HRQOL was not feasible due to limited prior data.

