#### Secondary study parameter(s)

Time-to-diagnosisTime-to-diagnosis will be defined as the period from the date of the index MRI result to the date of the start of the final treatment. A Kaplan–Meier analysis will be performed. Groups will be compared with use of the log-rank test.Overall survivalOverall survival will be defined as the period from the date of the index MRI result to the date of death. A Kaplan–Meier analysis will be performed. Groups will be compared with use of the log-rank test.Number of unnecessary treatment cyclesThe number of unnecessary treatment cycles of chemotherapy and bevacizumab will be calculated for both groups. The scores of both groups will be compared by means of the Mann–Whitney *U* test. Cost-effectivenessCost-effectiveness of the study arms will be determined from a societal perspective. Life years, QALYs, and costs will be assessed (See “Plans for assessment and collection of outcomes”). Direct and indirect costs will be included in the analysis. If benefits and costs are expected to persist beyond trial time horizon, a decision analytic model will be built. If not, a trial-based economic evaluation will be conducted.The cost-effectiveness analysis will be conducted in adherence to the 2024 version of the Dutch guidelines for economic evaluations [25].Outcome of the cost-effectiveness analysis will be expressed as incremental Costs, incremental Quality-Adjusted Life Years (QALY), and Incremental Cost-Effectiveness Ratio (ICER). The results of the cost-effectiveness analysis will be combined with observed and extrapolated uptake to estimate the budget impact over time. The budget impact analysis (BIA) will be performed according to the Dutch guidelines and the BIA guideline (“BIA leidraad”) and BIA calculation tool will be utilized [29].Health-related quality of lifeThe secondary outcome HRQOL will be captured and assessed as a continuous measure by EORTC QLQ-C30 and BN20 questionnaires through timepoint analyses at *t* = 6 weeks and *t* = 6 months. Compound scores will be calculated for each patient according to the standard scoring algorithms for these questionnaires [21, 23]. Group comparisons at these timepoints will be conducted using Student’s *t* tests. Results will be interpreted in terms of statistically significant difference and clinical relevance between study arms. Statistical difference will be assessed via a two-sided *p*-value ≤ 0.05. Additionally, secondary HRQOL will be evaluated longitudinally as a continuous measure using a mixed model for repeated-measures analysis, examining changes in individual patients’ raw scores over time. Previous literature indicates HRQOL analyses become unreliable when the response rate falls below 60% of all participants [30]. Should this occur, data analysis will be limited to the timepoints that meet the 60% response criterion.PET characteristics to predict clinical outcomeIn the intervention arm, we will perform exploratory analyses of the PET characteristics, both from static and (if available) dynamic PET images, such as SUV values and SUV ratio’s, as predictors of overall survival and progression-free survival, by cox analyses.Other study parametersLastly, determinants of unnecessary interventions will be investigated, including effect modifiers of the effect of [^18^F]FET PET on outcome. In order to answer this research question, a multivariable logistic regression analysis will be performed.

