### Methods in analysis to handle protocol non-adherence and any statistical methods to handle missing data {20c}

In case more than 10% of the patients in the intervention arm do not undergo the [^18^F]FET PET scan, an additional per-protocol analysis will be performed. This traditional per-protocol analysis will be supplemented by an instrumental variable analysis in which the complier average causal effect (CACE) will be estimated for the subpopulation of patients undergoing the extra [^18^F]FET PET scan. For the primary outcome measure of unnecessary interventions, no, or minimal missing data are expected, as data are all available in the electronic patient files. Dedicated study-specific data acquisition is performed by study personnel. Due to the organization of Dutch healthcare, loss to follow-up of patients is minimal. However, in the event that missing data do occur, imputation will not be applied to the primary outcome measure; (multiple) imputation is not considered to be optimally reliable or appropriate due to the nature of this outcome and its limited predictability. The occurrence of unnecessary treatments is highly dependent on contextual factors, such as physician decision-making and the clinical course of the illness, which makes accurate imputation difficult and potentially misleading. Therefore, for this specific outcome, an available-case analysis will be conducted including only those participants with available primary outcome data—expected to be all, or virtually all randomized patients. Where appropriate, sensitivity analyses will be performed to evaluate the robustness of the findings.

Regarding the HRQOL outcomes, standards of the field will be followed by using methods that are robust to missing data, e.g., linear mixed modeling combined with single-timepoint analyses.

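### The 60% response rule for secondary HRQOL can drop a whole visit, with the mixed model not exempted and deaths left in the literal denominator

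*Protocol article*

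**What the plan says.** The rule stands under Secondary study parameter(s), in the HRQOL paragraph. That paragraph first plans t tests at 6 weeks and 6 months. It then says "secondary HRQOL will be evaluated longitudinally as a continuous measure using a mixed model for repeated-measures analysis". The next two sentences set the rule: "Previous literature indicates HRQOL analyses become unreliable when the response rate falls below 60% of all participants", and in that event "data analysis will be limited to the timepoints that meet the 60% response criterion". No method is exempted, and the text does not say how patients who have died enter the response rate.

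The section on non-adherence and missing data {20c} commits the HRQOL outcomes to "using methods that are robust to missing data, e.g., linear mixed modeling combined with single-timepoint analyses".

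The week-12 co-primary comparison is specified separately, under Primary study parameter(s), with no response threshold. Sample size {14} says of that endpoint that "drop-out due to missing questionnaire data is estimated at 10" percent. Two further places bear on survival. Exclusion criteria rule out "Life expectancy of less than 6 months, determined by the treating physician", and Adverse event reporting and harms {22} lists death from tumor progression among the expected serious events.

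**The concern.** A likelihood-based mixed model is chosen because it uses whatever has been observed and does not need complete data at each visit. A rule that removes a whole visit once response is low withholds data from that model at exactly the visit where its robustness is needed.

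The denominator makes this worse. In glioblastoma the number of forms returned at 6 months depends on how many patients are alive as well as on how well the living comply. If the rate is taken over everyone randomized, mortality alone can push it under 60%. A post-randomization event, and one that is itself a secondary outcome (overall survival), would then decide whether a named HRQOL outcome is reported.

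Month 6 is the exposed visit. It is one of only two timepoints named for HRQOL in the Secondary objectives, so losing it leaves week 6 as the only secondary timepoint.

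**Working it through.** The 60% figure is taken from cited literature and has no derivation in the protocol to reproduce. What can be checked is when the rule triggers.

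**Inputs from the protocol:** 144 randomized, 72 per arm (Sample size {14}); threshold 60% of all participants (Secondary study parameter(s)); 10% missing forms at week 12 (Sample size {14}).

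**Assumed, because the protocol gives no figure:** survival to the visit, s; completion among the living, r, from 75% to 90%.

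**1. Forms needed.** 0.60 × 144 = 86.4. With 87 forms the visit passes (87/144 = 60.4%); with 86 it fails (86/144 = 59.7%). The most that one failing visit can lose is therefore 86 forms.

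**2. Week 12 at the plan's own figure.** 0.90 × 144 = 129.6, about 130 forms, or 90%. The rule does not trigger.

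**3. Trigger over all randomized patients.** The rule triggers when s × r < 0.60, that is, when the share who have died exceeds 1 − 0.60/r.

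| Completion among the living, r | 0.60/r | Rule triggers when deaths exceed |
|---|---|---|
| 90% | 66.7% | 33.3% |
| 85% | 70.6% | 29.4% |
| 80% | 75.0% | 25.0% |
| 75% | 80.0% | 20.0% |

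**4. Trigger over the living.** The rate is then simply r, and the rule cannot trigger at any survival while r is at least 60%. For example, with 70% alive and 85% completion, the rate over all participants is 0.70 × 0.85 = 59.5% (about 86 forms, visit dropped). Among the living it is 85%.

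**5. Is month 6 really at risk?** Assume exponential survival from the index MRI with median m months, so that s = 0.5^(t/m), with t = 6 for month 6 and t = 2.8 for week 12.

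| Assumed median | Alive at month 6 | × 90% completion | × 80% completion | Week 12, × 90% | Week 12, × 80% |
|---|---|---|---|---|---|
| 8 months | 59.5% | 53.5% | 47.6% | 70.6% | 62.8% |
| 10 months | 66.0% | 59.4% | 52.8% | 74.1% | 65.9% |
| 12 months | 70.7% | 63.6% | 56.6% | 76.6% | 68.1% |

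The Introduction's median survival of 14–16 months describes the whole treated course, and patients enter at least 3 months after concomitant chemoradiation. Even if it were used as the median from the index MRI, survival at 6 months would be 74.3–77.1%. That gives 66.9–69.4% response at 90% completion, 59.4–61.7% at 80% and 55.7–57.8% at 75%. A trigger at month 6 is plausible but not certain. At week 12 it does not occur in any of the tabulated scenarios.

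**6. Does about 59% response by itself spoil a mixed model?** A simulation used 72 per arm, four visits, an assumed correlation of 0.6 between visits, a true month-6 difference of zero, and month-6 dropout that depended on the week-12 score, more strongly in one arm. About 59% of month-6 forms were returned. The available-case difference, which is what a t test uses, was biased by −0.17 SD. The likelihood-type estimate was biased by −0.005 SD, with an empirical standard error of 0.20 SD. Dropout was missing at random by construction, so this shows only that a low rate alone does not invalidate the model.

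**The case against.** The case for the rule as it stands is fair in several respects. It is specified in advance, numeric, blind to the treatment effect and supported by a citation. Forms lost through neurological decline or death may well not be missing at random, so a reliability floor is defensible, and the simulation above does not settle that point. This part stands, but it argues for reporting a low-response visit with a caution. It does not require deleting the visit.

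A reader might infer four stronger things that the document does not support:

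- **That the plan counts deaths as non-response.** It never says so. This follows only from a literal reading of an unqualified denominator.
- **That the rule would remove the week-12 co-primary analysis.** It stands under the secondary HRQOL text, while the week-12 test is set out elsewhere without a threshold. Because the rule speaks of HRQOL analyses in general, its reach deserves a clarifying sentence, but no more.
- **That the rule contradicts the mixed model.** There is tension, not contradiction. The model could still be fitted to the remaining visits, and the missing-data section names it as an example, "linear mixed modeling combined with single-timepoint analyses".
- **That data will be lost.** The loss is conditional on survival and completion rates that the protocol does not give, and the exclusion of short life expectancy lowers the risk.

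**Conclusion.** The concern holds for secondary HRQOL, chiefly at month 6. As written, the rule does not exempt the mixed model, and its literal denominator lets mortality drop a visit despite good completion among survivors. The trigger lies at about 29%, 25% or 20% deaths for completion of 85%, 80% or 75%, and at most 86 returned forms would go unused at a failing visit. Whether the trigger is reached rests on assumed survival and completion. With 90% completion, assumed medians of 8 to 12 months put month-6 response at 53.5% to 63.6%, on both sides of the threshold. The first co-primary outcome is not affected, and at the plan's own 10% missingness neither is the week-12 HRQOL comparison. This is a worthwhile, inexpensive improvement to a stated rule and does not threaten the primary conclusions.

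**What to change.** Replace the rule in the secondary HRQOL paragraph with text to this effect:

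- All observed visits stay in the mixed model, whatever the response rate.
- The response rate at each visit is calculated among patients who are alive and due a form, with the number of deaths reported beside it.
- A rate below 60% flags the single-timepoint comparison at that visit as low-reliability and does not remove it.
- The rule does not apply to the week-12 co-primary analysis.

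The cost is a few lines in the protocol or analysis plan. Recruitment is expected to run to December 2027, so the change can be made before analysis. The downside is that estimates at low-response visits will appear in the report and must carry a caution, because dropout there may not be missing at random.

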
### Interim analyses {21b}

Not applicable, we will not perform an interim analysis as this could lead to inaccurate estimations of the intervention effect.

### Methods for additional analyses (e.g., subgroup analyses) {20b}

As treatment center will be used for stratification and it is expected that some of the centers will recruit small numbers of patients, no adjusting for this stratification factor will be performed in the primary analysis. However, a correction analysis for treatment center will be performed as sensitivity analysis. In addition, correction analyses for MGMT promoter methylation status (methylated versus unmethylated versus unknown), Karnofsky performance score (< 70 vs ≥ 70), and prior surgical procedure (biopsy versus resection) will be performed as sensitivity analyses [31].

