## Assignment of interventions: allocation

### Sequence generation {16a}

The computer-based randomization tool Ldot ® (by MEMIC, Maastricht University, https://www.ldot.nl/) will be used. Block randomization will be done with stratification by treatment center.

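### Randomization is stratified by centre but the primary test is not: to the extent that centres differ in risk, the planned Z test is conservative and gives up some power

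*Protocol article*

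**What the plan says.** Sequence generation {16a}: "Block randomization will be done with stratification by treatment center". Study setting {9} lists eight centres, six academic and two non-academic.

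Statistical methods {20a}: the first co-primary outcome, any unnecessary intervention (yes/no), is compared between arms by a two-sided Z test with pooled variance at alpha 0.05. Centre does not enter.

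Methods for additional analyses {20b}: because some centres are expected to recruit few patients, "no adjusting for this stratification factor will be performed in the primary analysis". The next sentence plans a centre-corrected analysis as a sensitivity analysis.

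Sample size {14}: the two primary endpoints are tested in fixed sequence. If unnecessary interventions is not significant, HRQOL becomes exploratory.

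**The concern.** Balancing the arms within centres removes most of the between-centre variation from the arm comparison. An unstratified test does not credit this, and its standard error still contains that variation. If centres differ in risk, the p-value is too large and the confidence interval too wide.

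The stated reason for not adjusting fits a regression with one term per centre, where small centres cause trouble. It does not fit Mantel-Haenszel methods, which pool within-centre comparisons and tolerate sparse strata.

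Some difference between centres is plausible. According to the Abstract, management is left to the local multidisciplinary board. Under {10} the treating physician decides which patients count as uncertain, and under {12} the treating physician helps classify the outcome. Section {20c} calls the outcome "highly dependent on contextual factors, such as physician decision-making and the clinical course of the illness".

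At stake is power for the endpoint that opens the HRQOL test. A significant centre-corrected sensitivity analysis could not open that gate, because the sequence runs on the primary test.

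**Working it through.** **1. Inputs from the article.** Control rate: "we estimate that 37% of the glioblastoma patients that meet our inclusion criteria". Intervention rate: about "12% from clinical scenarios". Test: "Using a two-sided *Z* test", that is, a "test with pooled variance with an alpha of 0.05, based on a power of 90" percent. Size: "we need 61 patients in each arm, so 122 in total", raised to 144 (72 per arm). Eight centres, 1:1 allocation.

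**2. The plan's own figure.** Mean rate (0.37 + 0.12)/2 = 0.245.

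n per arm = [1.960 × √(2 × 0.245 × 0.755) + 1.2816 × √(0.37 × 0.63 + 0.12 × 0.88)]² / 0.25²
= [1.960 × 0.6082 + 1.2816 × 0.5820]² / 0.0625
= (1.192 + 0.746)² / 0.0625 ≈ 60.1, rounded up to 61.

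The stated 61 reproduces. Power at 72 per arm: (0.25 × √72 − 1.192)/0.5820 = 1.597, which gives 94.5%.

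**3. Why the Z test can be conservative.** Under the null the pooled variance is p(1−p)(1/n₁ + 1/n₂). Here p(1−p) equals the average within-centre p_k(1−p_k) plus the between-centre variance of p_k. Blocking within centre takes most of the second term out of the true sampling variance, but the pooled formula keeps it. If all p_k are equal, that term is zero and the test is at its nominal level.

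The Cochran-Mantel-Haenszel (CMH) statistic uses within-centre variation only:

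Σ(x_k − m_k t_k/N_k) / √Σ[t_k c_k m_k(N_k − m_k) / (N_k²(N_k − 1))]

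with t_k and c_k patients per arm, N_k patients and m_k events in centre k, and x_k events in the PET arm. A centre with patients in one arm only contributes nothing.

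**4. Simulation assumptions.** The article gives no block size, centre sizes or between-centre variation. Assumed: permuted blocks of 4; either eight centres of 18, or skewed sizes 40/30/24/18/12/10/6/4; normal centre effects on the logit scale with SD s; marginal rates held fixed; no continuity correction; 40,000 trials per cell. Monte Carlo standard error at 5%: √(0.05 × 0.95/40,000) = 0.11 points.

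**5. Type I error, common rate 37% (equal / skewed centres).**

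| s | Centre rates, 10th–90th percentile | Z test | CMH |
|---|---|---|---|
| 0 | 37% | 5.0 / 5.2% | 4.9 / 5.1% |
| 0.5 | 23–52% | 4.6 / 4.4% | 5.0 / 4.9% |
| 0.8 | 16–60% | 4.0 / 3.9% | 4.9 / 4.8% |
| 1.0 | 13–66% | 3.7 / 3.8% | 5.0 / 5.0% |
| 1.5 | 6–76% | 2.5 / 2.7% | 4.9 / 5.0% |

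A repeat simulation with blocks of 4 and skewed centres, again including centres of 4 and 6 patients, gave 5.0%, 4.6%, 3.7% and 2.8% for Z at s = 0, 0.5, 1.0 and 1.5, and 4.9–5.1% for CMH.

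**6. Power, Z → CMH.** The first two columns give equal / skewed centres. The last comes from 20,000 trials with centre sizes 36/28/24/18/14/10/8/6.

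| s | 37% vs 12% (design) | 37% vs 17% | 34% vs 16% |
|---|---|---|---|
| 0 | 95.0→94.7 / 95.0→94.8 | 78.5→78.0 / 78.8→78.2 | 72.1→71.4 |
| 0.5 | 95.3→95.5 / 95.2→95.3 | 79.1→79.6 / 78.7→79.4 | 72.1→72.8 |
| 1.0 | 95.5→96.6 / 95.2→96.2 | 80.1→83.5 / 80.1→83.3 | 72.8→76.8 |
| 1.5 | 95.5→97.6 / 95.0→97.1 | 80.2→87.3 / 80.4→86.7 | 74.0→81.2 |

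From unrounded results, the CMH gain at the design effect is −0.2 points at s = 0, +0.1 to +0.2 at 0.5, about +1.0 at 1.0 and +2.0 to +2.1 at 1.5. For the smaller effects it is −0.5 to −0.7, +0.6 to +0.7, +3.3 to +4.0 and +6.4 to +7.2. At s = 0.3 (centre rates 28–46%) CMH was still 0.1 to 0.2 points behind, so break-even lies between 0.3 and 0.5.

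**The case against.** The strongest reply is that this is a choice between two valid analyses. The plan's choice is prespecified and explained, it matches the test used for the sample size, and any error is toward a type I rate below 5%. Centre is not ignored either, since {20b} plans a corrected sensitivity analysis. All of that stands.

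It also stands that the evidence for centre differences is indirect. The remark in {20c} about physician decision-making explains why individual outcomes are hard to impute; it does not say that risk varies by centre. Central PET review under {18a} may narrow differences in the PET arm. An SD of 1.5 is extreme, and the losses of several points need both large heterogeneity and a true effect smaller than planned.

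Two things do not stand. Small centres are not a reason against Mantel-Haenszel, as the skewed simulations show. And the planned sensitivity analysis does not recover the lost power, because it has no role in the gate. A smaller effect is also not far-fetched: the 37% comes from a survey of the centres and the 12% from clinical scenarios.

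**Conclusion.** This is a modest efficiency point, conditional on centres differing in outcome risk. If they differ moderately to strongly (SD 0.5 to 1.5), the planned test runs at about 4.6% to 2.8% instead of 5%. It gives up 0.1 to 2 points of power at the design effect, and about 3 to 4 points at SD 1.0 or 6 to 7 at SD 1.5 if the true effect is smaller. The SDs, centre sizes and block size are assumptions.

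A reader might infer more than the article supports:
- That the test is conservative whatever happens. With no centre effect it holds its nominal level.
- That the trial is underpowered or its result invalid. Power at the design effect is near 95%, and the error is on the safe side.
- That stratifying is free. It costs 0.2 to 0.7 points if centres do not differ.
- That the HRQOL analysis also needs a centre effect. Nothing here examines that outcome.

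**What to change.** In {20a} and {20b}, swap the two roles. Make the primary analysis of unnecessary interventions a Cochran-Mantel-Haenszel test stratified by centre, without continuity correction, reported with the Mantel-Haenszel risk difference and its 95% CI. State that this test opens the HRQOL test. Keep the unstratified pooled Z test as the sensitivity analysis.

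Name the variance estimator for the interval (the simulations checked the test, not the interval), and say that a centre with patients in one arm only contributes nothing. The estimand hardly moves: the Mantel-Haenszel weight t_k c_k/N_k equals N_k/4 under exact 1:1 allocation, so centres count in proportion to their size.

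The cost is a sentence or two, a report to the ethics committee and a registry update under {25}, and the small power loss if centres do not differ. The sample size can stay. Recruitment is expected to run to December 2027 and no interim analysis is planned, so the change can be prespecified before any comparison of the arms.
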